In Orlando, Florida evidence suggests that the more passengers a driver carries, the lesser the likelihood of being involved in a road traffic crash [8].This is because the driver’s behavior or attitude would either be self-regulated and/or the passengers would engage the driver if he is driving in an undesirable manner. In Spain, the passing of legislation that increased the likelihood of being jailed for any committed traffic offence significantly reduced the incidence of road traffic crashes [9]. Interestingly, the impact of this legislation intervention had longer lasting effects sustained beyond 3 years [10]. In general however, there are mixed results on the impact of increased law enforcement such as alcohol checks on road traffic crashes depending on the context in which the intervention is evaluated [11–15]. Similarly, there are mixed results on the impact that road safety education programs have on the incidence of road traffic crashes [16–19].

In spite of the dearth of literature on effective interventions that reduce road traffic crashes in developing countries settings, an innovative randomized control trial was conducted in Kenya to test the impact of placing stickers in PSV minibuses encouraging passengers to speak out against dangerous driving [20]. After a period of 8 months, insurance claims rates from PSV minibus road traffic crashes fell by over 50% for minibuses with the stickers compared to those without. Similar studies are now being carried out in Tanzania, Uganda, and Rwanda, and generating context specific evidence would be useful for Zambia as well [21].

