### Study design

This evaluation will be a stratified two-arm randomized controlled trial with a one-to-one ratio as illustrated in Fig. 3. We will stratify based on vehicle type, thus creating a two-arm trial for minibuses and a separate two-arm trial for big buses.

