### Sample size and selection

For a conservative measure of effect, and thus a more conservative and larger sample size, we propose a difference-in-difference primary analysis examining data from 7 months before compared to the 7 months after the implementation of the intervention (and not disaggregated into monthly measures). Based on budget constraints and logistics, we estimated the minimal person time for minibuses assuming we would like to see a minimal effect of 0.01 absolute difference in the *change* in the accident rate per 1000 minibuses over the 14-month period (7-month pre vs. 7-month post). This change is similar to that of the Kenya study. Table 1 presents the inputs used for this equation, assuming the accident rate reported within the Kenya study among the controls would be generalizable to Zambia [20]. To account for potential spillover due to the fact that passengers will transfer between buses (though we assume drivers to remain within the same buses), we assumed that the control arm would have slight improvement in the accident rate over the 14-months observed. Additionally, the equation assumes an alpha of 0.05 and power (beta) of 80%. The equation used is as follows [22]:$$ N\  person- years\ in\ each\  arm={\left({Z}_{\frac{\alpha }{2}}+{Z}_{\beta}\right)}^2\Big[\left({\lambda}_0+{\lambda}_1\right)/{\left({\lambda}_0-{\lambda}_1\right)}^2 $$

**Table 1 Tab1:** Sample size calculation parameters

Z_a/2_	Type I error	1.96
Z_B_	Type II error	0.84
*λ* _0_	Estimated change in the accident rate per 1000 minibuses over the 14-month period in the control arm	−0.01
	Absolute difference	.01
*λ* _1_	Estimated change in the accident rate per 1000 minibuses over the 14-month period in the intervention arm	−0.02
y	Number of person years in each arm	116
	Number of cars assuming cars followed for 1.16 years or 14 months	954
	Number of vehicles to follow with 10% buffer per arm	1060

The sample size calculation formula in Table 1 used is adopted from Hayes & Mouton (2009). A buffer of 10% was included to allow for buses that may drop out of the study during recruitment for any reason

For the big buses, there is a finite sample of buses and we intend to enroll all big buses from within the sampled areas.

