## Discussion

Given the potential infrequency of overall RTCs (0.026 per 1000 minibuses per 6 months as reported in Kenya) and the relatively short length of the study, it is possible we will not find an impact at 7 months. There is a risk that our effect may be conservatively estimated both due to the ITT analysis but also due to potential spillover effects as passengers may go between the arms of the study; however, we feel confident there may still be a potential impact of the new RTSA road safety sticker. This is because the Kenya study similarly randomized sticker placement within the same city, thus allowing for spillover, and was able to see an impact of the sticker program. Additionally, though in the sample size calculation, we accounted for a potential improvement in the accident rate over the 14-months examined in the control group, and estimate we still anticipate some spillover thus resulting in conservative effect estimation.

Though every PSV operator is mandated by law to have valid insurance cover, the use of insurance claims data for our outcome could lead to some measurement error as not everyone files insurance claims when involved in a crash. This may be primarily prevalent in those with third party insurance who may be involved in a crash with unclaimed physical objects such as trees, walk ways, barricades etc. However, RTCs involving injuries or deaths to passengers are highly likely to be reported to insurance companies.

The outcomes, analysis, and recommendations of this evaluation are expected to inform the national scale-up of the new RTSA road safety bus stickers in PSVs by RTSA. Specifically, the results will help RTSA to understand whether the toll-free bus sticker has an impact and whether the new RTSA road safety bus stickers can improve on road safety outcomes. If only limited changes are observed, then RTSA and other national road safety stakeholders will collaborate to understand the reasons and propose further adjustments.

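### The sample size is said to account for spillover, but Table 1 moves both arms by 0.01 and leaves the 0.01 contrast unreduced

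*Protocol article*

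**What the plan says.** Sample size and selection sets the minibus target first: "we would like to see a minimal effect of 0.01 absolute difference in the" change in accident rate, 7 months before against 7 months after. It calls this similar to the Kenya result. It then introduces the spillover allowance ("To account for potential spillover due to the fact that passengers will transfer between buses"), under which the control arm is assumed to improve slightly.

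Table 1 gives three figures:
- "Estimated change in the accident rate per 1000 minibuses over the 14-month period in the control arm": -0.01.
- Absolute difference: 0.01.
- "Estimated change in the accident rate per 1000 minibuses over the 14-month period in the intervention arm": -0.02.

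The Discussion returns to the allowance, saying that in the sample size "we accounted for a potential improvement in the accident rate over the 14-months examined in the control group". In the same place it still expects some spillover and conservative estimates. It also notes that the Kenya trial randomized within one city, so spillover was possible there too. The Background gives the Kenya effect: "insurance claims rates from PSV minibus road traffic crashes fell by over 50% for minibuses with the stickers compared to those without".

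**The concern.** If passengers carry the sticker's influence into control buses, the observed contrast is the total sticker effect minus what the controls gained. A sample size that allows for this must be computed on a smaller contrast. In Table 1 the contrast with the allowance equals the target set before it, so the control gain has been matched by a larger assumed fall in sticker buses.

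The control shift would be coherent as a secular trend common to both arms, which difference-in-difference removes. The plan, however, attributes it to spillover.

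Odd- and even-plate buses run in the same towns, the plan expects passengers to move between them, and the result is meant to inform a national scale-up. Readers are told that the sample size has a protection it does not have.

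**Working it through.** **Inputs.** From Sample size and selection: "the equation assumes an alpha of 0.05 and power (beta) of 80" per cent, with 1.96 and 0.84 in Table 1, so (1.96 + 0.84)² = 7.84; changes of -0.01 and -0.02. From Study design: "stratified two-arm randomized controlled trial with a one-to-one ratio". From the Discussion: 0.026 per 6 months in Kenya, which Sample size and selection carries over to Zambia. *Assumption:* 0.026 is a rate per bus, although it is labelled per 1000 minibuses. If constant, the 7-month rate is 0.026 × 7/6 = 0.0303.

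**1. The plan's own figure.** The printed formula is N = 7.84 × (λ0 + λ1)/(λ0 − λ1)². With Table 1 inputs in absolute value, N = 7.84 × 0.03/0.0001 = 2352 person-years per arm (-2352 with the signs kept). At 1.16 years per bus that is 2028 buses. Neither 116 person-years nor 954 buses results. That is a separate fault, and correcting the arithmetic would leave the present point unchanged. It does mean that what the allowance cost in the plan's actual N cannot be known.

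**2. The contrast.** With the allowance: 0.02 − 0.01 = 0.01. Target set before it: 0.01. Reduction for contamination: zero.

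**3. What the pair implies.** If the control fall is leaked benefit, the total fall in sticker buses is 0.02, and 0.01/0.02 = 50% of it reaches controls.

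| Base rate | Fall in sticker buses | Fall in control buses | Sticker vs control, post period |
|---|---|---|---|
| 0.0303 (7 months) | 0.02/0.0303 = 66% | 0.01/0.0303 = 33% | 0.0103 vs 0.0203: 49% lower |
| 0.026 (6 months) | 77% | 38% | 0.006 vs 0.016: 62.5% lower |
| 0.052 (if the λ are annual) | 38% | 19% | 0.032 vs 0.042: 24% lower |

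The 7-month row fits best, because the text compares 7 months with 7 months. A fall of a third in controls is not slight.

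**4. Effect of the shift on size, using event rates.** For a Poisson difference-in-difference with independent periods, buses per arm = 7.84 × (sum of the four cell rates)/contrast².
- Base 0.026, changes 0 and -0.01: 7.84 × 0.094/0.0001 = 7370. Changes -0.01 and -0.02: 7.84 × 0.074/0.0001 = 5802.
- Base 0.0303, same two cases: 8729 and 7161.

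The shift lowers the sum of rates by 0.02 at a fixed contrast, so the requirement falls by 7.84 × 0.02/0.0001 = 1568 buses per arm on either base. Only this direction is used here; the gap between these sizes and 954 is a different matter.

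**5. Effect of the shift in the printed formula.** Changes 0 and 0.01 give 784 person-years; 0.01 and 0.02 give 2352. This is a rise of 1568, the same quantity with the opposite sign, and it arises only because the numerator adds changes where rates belong. The unshifted pair (0, -0.01) is inferred from the stated target; the article does not print it.

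**6. Labelled scenario, not an estimate.** Suppose the total effect is 50% of the 7-month rate (0.0152) and controls gain the plan's 0.01. The contrast is 0.0052 and the size grows by about (0.01/0.0052)² = 3.7 times. With a total of 60% (0.0182), the contrast is 0.0082 and the factor is 1.5.

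**The case against.** The strongest reply is that 0.01 is already a net target. It is defined as a between-arm difference and likened to Kenya, where the Discussion says spillover was also possible. The implied post-period contrast of about 49% is close to the Kenya figure of over 50% versus control. This stands as a defence of the number 0.01. It does not rescue the claim: if 0.01 is already net, no control shift was needed, and the shift still does not account for anything.

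Four stronger readings are tempting, and the documents do not support them:
- *The sticker must cut crashes by 66-77% for the trial to succeed.* That is the assumed pre-post fall within sticker buses, on an assumed unit. The tested contrast is about 49-63% versus control on the same bases, and on an annual scale the within-arm fall is 38%.
- *The allowance costs nothing.* This is true of the contrast but not of the printed formula, whose output triples.
- *The trial should expect a contrast of 0.005-0.008.* This treats Kenya's between-arm effect as a total effect and subtracts spillover a second time. The 60% case appears nowhere in the article.
- *The article would present a null as evidence against the sticker.* The Discussion already says that an impact may not be found at 7 months and that spillover makes the estimate conservative. What it lacks is the link to the sizing: under the assumed spillover, a smaller total effect puts the contrast below the 0.01 used.

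**Conclusion.** The point holds as a misstatement about the sample size. The allowance described in Sample size and selection and repeated in the Discussion takes nothing off the 0.01 contrast, and with rates in the variance it makes the requirement smaller by 1568 buses per arm, so it is not conservative. The plan's own explanation implies a total fall of 0.02 in sticker buses and 0.01 in controls, about 66% and 33% of a 7-month rate.

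The lack of any reduction in the contrast can be read directly from Table 1 and needs no assumption. The percentages assume that the λ and 0.026 are on the same scale, with 7-month periods. The bus counts assume a per-bus Poisson rate and independent periods, though the direction does not depend on the base rate. The target of 0.01 is not itself shown to be wrong.

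**What to change.** In Sample size and selection, Table 1 and the Discussion:

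1. Delete the statement that the sample size accounts for spillover.
2. State that 0.01 is the net between-arm difference after any spillover, of a size taken from a Kenya trial that was itself exposed to same-city spillover.
3. If the control change of -0.01 is kept as spillover, state the total fall in sticker buses that it implies (0.02), and do not call the control gain slight.
4. Add to the Discussion that, if the total effect is smaller under that spillover, the contrast falls below the 0.01 for which the trial was sized, so a null result would not exclude a sticker effect.

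Do not print 0.005-0.008 as the expected contrast; at most show it as a labelled scenario with its assumptions.

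The cost is wording and one restated figure. No more buses are needed for this change. The downside is that the stated detectable effect looks less favourable.

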### Randomization

To randomize the sticker placement, RTSA will place the new RTSA road safety sticker only in buses with license plates ending with an odd number (intervention arm) while buses with a license plate ending with an even number will be considered for the control arm. To reach the suggested 954 per arm, we will aim to enroll approximately 1060 buses per arm, allowing for 10% drop out for any reason.

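### Table 1 does not support the stated 80% power: it does not reproduce from its own inputs, and its formula does not fit the planned difference-in-difference analysis

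*Protocol article*

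**What the plan says.** Under Sample size and selection, the protocol article proposes a difference-in-difference of the 7 months before against the 7 months after sticker placement. It targets a "minimal effect of 0.01 absolute difference in the" change between arms. It states that "the equation assumes an alpha of 0.05 and power (beta) of 80" percent, and prints a formula for person-years per arm: (Zα/2 + Zβ)² × (λ0 + λ1)/(λ0 − λ1)².

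Table 1 gives these rows:
- λ0, "Estimated change in the accident rate per 1000 minibuses over the 14-month period in the control arm": -0.01
- λ1, "Estimated change in the accident rate per 1000 minibuses over the 14-month period in the intervention arm": -0.02
- observation time required per arm, in bus-years: 116
- minibuses per arm, labelled "Number of cars assuming cars followed for 1.16 years or 14 months": 954
- minibuses per arm once the buffer is added: 1060

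The Randomization section repeats the result: "To reach the suggested 954 per arm, we will aim to enroll approximately 1060 buses per arm". The same sample size section says that the Kenya control rate is assumed to carry over to Zambia. The Discussion gives that rate as 0.026 per 1000 minibuses per 6 months. The Data analysis section makes the sticker-by-post interaction the main estimate, on a yes/no crash outcome, with standard errors clustered by bus.

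**The concern.** There are two separate problems. The table's outputs do not follow from its inputs or from one another. And the formula, even if computed correctly, is not the one for the planned estimate. Its numerator, λ0 + λ1, is the variance of two independent Poisson rates, and works only because a Poisson rate is its own variance. A change in a rate is not its own variance, and a negative change makes the numerator negative.

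The results are expected to inform a decision on national scale-up. If the 80% figure stays in print, a null result could be read as evidence that the stickers do not work, when the design had little chance of detecting the effect it names.

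**Working it through.** **1. The plan's own formula with its own inputs.** From Table 1: Zα/2 = 1.96, Zβ = 0.84, λ0 = -0.01, λ1 = -0.02.

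- (1.96 + 0.84)² = 7.84.
- 7.84 × (-0.03)/(0.01)² = -2352 person-years, which is impossible. In absolute value it is 2352.
- 2352/1.16 = 2028 buses, or 2016 at 14/12 years. Dividing by 0.9 for the buffer gives 2253 or 2240.
- Table 1 states 116, 954 and 1060.

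One-sided alpha (1855 person-years), 90% power (3152) and a two-proportion formula (2319 per arm, or 2515 with continuity correction) do not give the printed figures either.

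**2. The rows against each other.** 116/1.16 = 100 buses, not 954. Conversely, 954 × 1.16 = 1107 person-years, not 116. Only the last step reproduces: 954/0.9 = 1060.

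**3. Power on the plan's own formula.** Taking the inputs as exact and in absolute value, 1107 person-years give Φ(√(1107 × 0.0001/0.03) − 1.96) = Φ(1.92 − 1.96) = 48%.

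**4. Power for the planned difference-in-difference.** Let b be the pre-period rate in both arms. The post-period rates are then b − 0.01 (control) and b − 0.02 (intervention), following Table 1.

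Variance = [sum of the four values p(1 − p) − 2ρ × (sum over arms of √(pre variance × post variance))]/n, where ρ is the correlation between a bus's two periods. Power = Φ(0.01/SE − 1.96).

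Assumptions: rates and changes are per bus per 7 months; b = 0.026 × 7/6 = 0.0303; n = 954.

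- Cell variances: 0.0294 (twice), 0.0199 and 0.0102, which sum to 0.0890.
- ρ = 0: SE = √(0.0890/954) = 0.0097; power = Φ(1.035 − 1.96) = 18%.
- ρ = 0.3: the variance sum falls to 0.0640; SE = 0.0082; power = 23%.
- ρ = 0.5: the variance sum falls to 0.0474; SE = 0.0070; power = 29%.

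Varying the baseline and the number of buses:

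| Baseline b | ρ = 0, n = 954 | ρ = 0.5, n = 954 | ρ = 0.5, n = 1060 |
|---|---|---|---|
| 0.02 | 29% | 38% | 41% |
| 0.026 | 21% | 34% | 37% |
| 0.0303 | 18% | 29% | 32% |
| 0.04 | 14% | 23% | 25% |
| 0.05 | 12% | 19% | 20% |

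The top row is an extreme: at b = 0.02 the post-period intervention rate is exactly zero.

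**5. The printed unit taken literally.** If 0.0303 and 0.01 are per 1000 minibuses, the expected number of crashes over both arms and both periods is 954 × (4 × 0.0303 − 0.03)/1000 = 0.087, or 0.097 with 1060 per arm. Power is then about 5%, the type I error rate.

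**6. The largest effect possible in this scenario.** With b = 0.0303 the control post rate is 0.0203, so the difference in change cannot exceed 0.0203, which means no crashes at all in the intervention arm. The variance sum is then 2 × 0.0294 + 0.0199 = 0.0787; SE = √(0.0787/954) = 0.0091; power = Φ(2.24 − 1.96) = 61% at ρ = 0.

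**The case against.** The strongest defence is that the table may be a faulty report of a sound calculation. The inputs are printed to one significant digit, and N varies with the inverse square of their difference. Absolute inputs of 0.0056 and 0.0187 round to the printed values and give 7.84 × 0.0243/0.0131² = 1110 person-years, close to 954 buses. Plain rates of 0.010 and 0.026 give 7.84 × 0.036/0.016² = 1102 person-years, or 950 buses at 1.16 years. And 116 could be a misprint of 1116, since 1116/1.17 = 954. This much stands: a reader might infer that the correct size is 2016 to 2028 buses, but that is only what the printed inputs yield, not a valid requirement. None of these explanations is documented, though, and none rescues the power of the difference-in-difference, because all keep the two-rate formula.

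The article also says that the size was set under budget and logistic constraints, and the Discussion concedes that no impact may be found at 7 months. So the documents do not show that the sponsor counts on a null being informative. But neither statement withdraws the 80%.

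Counting all 14 months is not a further error. A difference-in-difference uses the pre-period data; the fault lies in the formula to which they were supplied.

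**Conclusion.** The point holds. Non-reproduction and the mismatch between formula and analysis follow from the article alone. The size of the power shortfall rests on assumptions: rates per bus rather than per 1000, the Kenya rate scaled from 6 to 7 months, and a within-bus correlation that the article does not give. On these, power for a 0.01 difference in change at 954 per arm is about 18% to 29% for correlations from 0 to 0.5. It is roughly 12% to 41% over baselines of 0.02 to 0.05 and 954 to 1060 buses, well below 80% throughout.

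Two stronger readings are not supported. A reader might quote 18% as the power of the trial, but that is one corner of the range, with independent periods. A reader might also multiply 2.8 by the SE of 0.0097 and report 0.027, about 89% of baseline, as the difference detectable at 80% power. That exceeds the control post rate of 0.0203 and would need a negative crash rate in the intervention arm. The supportable statement is that, in this scenario with 954 per arm and independent periods, no attainable effect reaches 80%.

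**What to change.** - Replace Table 1 with a calculation that starts from the pre and post crash rates in each arm per 7 months. It should use the variance of the planned difference-in-difference and state the within-bus correlation assumed.
- Correct the unit label, so that the rates and the 0.01 target are on one explicit scale.
- Delete the 80% claim and state the resulting power at 954 per arm as a range, with the baseline rates and correlations behind it. Do not print a single figure or the 0.027 detectable difference.

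The cost is a rewritten table and paragraph and a less favourable stated power. No change in enrolment is needed: budget and logistics are a legitimate reason for 954 per arm, provided that the power is stated for that number.

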### Randomization

To randomize the sticker placement, RTSA will place the new RTSA road safety sticker only in buses with license plates ending with an odd number (intervention arm) while buses with a license plate ending with an even number will be considered for the control arm. To reach the suggested 954 per arm, we will aim to enroll approximately 1060 buses per arm, allowing for 10% drop out for any reason.

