### Intervention: New RTSA road safety bus sticker

For the intervention arm of the study, RTSA will be responsible for distribution of the stickers as well as routine inspection of the vehicles to ensure that road safety bus stickers are continuously displayed throughout the evaluation. The stickers will be placed within minibuses and long distance big buses (seating capacity of at least 54 passengers).

In the minibuses, these stickers will be placed on the panels between the passenger window and the ceiling of the vehicle. Approximately six stickers will be placed in each minibus ensuring that at least one sticker is within eye view of each passenger in the vehicle. In the big buses, between 10 and 16 stickers will be placed in each and the placement will vary depending on the design and size of the bus. They could be placed on panels between the passenger window and the ceiling of the vehicle, behind the driver’s seat, or overhead above the televisions, as long as at least one is within eye view of each passenger.

Big buses are routinely inspected before they leave the central bus stations for their long distance journeys. Minibuses will be inspected during routine RTSA road checks, within bus stations and during regular RTSA vehicle inspections. The road safety bus stickers’ campaign and monitoring of minibuses and big buses will occur for approximately 7 months.

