#### RTSA data and police reports

As the government body mandated to register and license drivers, motor vehicles and commercial vehicle operators, RTSA maintains records of all PSVs. Any additional data required for analysis will be retrieved from RTSA. In addition, if available and timely, police reports on motor vehicle road traffic crashes for the study period will also be retrieved for analysis.

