We will run the difference-in-difference analysis assuming intent-to-treat (ITT), in that all of those who received the assigned new RTSA road safety bus sticker (even vs. odd) will have placed the new RTSA road safety bus sticker accordingly. Though it is expected that the monitoring of RTSA will not provide perfect fidelity to the specific arms, the ITT analysis will provide a conservative estimate of effect.

Due to the nature of the study, drivers and participants cannot be blinded, however, it will be helpful to examine the effect of the new RTSA road safety bus stickers overtime to determine if Hawthorne effects, the process by which a subject of a study changes their behavior due to the knowledge that they are being surveyed and measured, reduces overtime (outcome 2). To this end the regression presented above will become a controlled interrupted time series (ITS) where each minibus will have an observation for each month for the 7-months before the intervention and 7-months after the sticker placement – a form of repeated measures analysis.

In sensitivity analysis, we will examine the difference between the study periods in our primary outcome (seven-month accident rate) controlling for baseline differences.

For outcomes with a comparison over time but not between the two study arms (outcome 4), we will run a general t-test comparison between the RTC rates before and after the intervention as well as a regression analysis controlling for any differences at baseline.

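### Allocation by odd/even plate is quasi-randomised and unconcealed, and nothing commits the analysis to minibuses lost during recruitment, so the enrolled arms can be selected differently

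*Protocol article*

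**What the plan says.** Study design describes a "stratified two-arm randomized controlled trial with a one-to-one ratio". The only allocation mechanism given is in Randomization: "RTSA will place the new RTSA road safety sticker only in buses with license plates ending with an odd number (intervention arm", and "buses with a license plate ending with an even number will be considered for the control arm". No random sequence and no concealment step is described.

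The Intervention section states that "RTSA will be responsible for distribution of the stickers as well as routine inspection of the vehicles", so the body that applies the plate rule also handles the stickers. Data analysis adds: "Due to the nature of the study, drivers and participants cannot be blinded".

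On losses, the footnote to Table 1 reads: "A buffer of 10% was included to allow for buses that may drop out of the study during recruitment for any reason". Randomization gives the numbers: "To reach the suggested 954 per arm, we will aim to enroll approximately 1060 buses per arm, allowing for 10% drop out for any reason". Sample size and selection limits this to minibuses in effect, because every big bus in the sampled areas is to be enrolled.

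The primary analysis is a difference-in-difference of the 7 months before and the 7 months after the intervention. It is labelled intention-to-treat, but the sentence that defines this is framed around buses that received their assigned sticker. It does not say that a bus lost during recruitment stays in the analysis.

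**The concern.** The last digit of a plate is fixed and visible before anyone contacts the bus. Staff cannot move a bus between arms, but they and any operator who knows the rule can tell the arm before deciding whether the bus takes part. Any loss during recruitment is then a loss after the arm is knowable. The demand on the two arms also differs, since only an odd-plate bus has to accept stickers.

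The primary outcome makes this matter more than usual, because the pre-intervention crash record is half of it. If buses that crashed in those 7 months were lost more often from one arm, that arm's before value would be too low. Its later rate would return towards the usual level, and the difference-in-difference would count that return as an effect. The estimate informs a national scale-up decision.

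**Working it through.** **The plan's own figure.** 954 / (1 - 0.10) = 1060 per arm, which reproduces. The allowance is 1060 - 954 = 106 minibuses per arm, for losses that can occur once the arm is knowable. This is a planning buffer and not a forecast.

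**Inputs for the illustration.**
- The Discussion gives a Kenyan rate of 0.026 per 6 months. Scaled to 7 months, p = 0.026 x 7/6 = 0.0303. The article states the rate per 1000 minibuses; I read it per bus, which is an assumption.
- The target difference is 0.01 (Table 1), read in the same units.
- q is the share of odd-plate buses with a pre-period crash that are lost, with no such loss from the even arm. The values 10%, 25% and 50% are assumptions with no source in the article.
- Post-period risk is taken as unrelated to the pre-period crash.

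**Formula.** Enrolled odd-arm pre-rate = p(1 - q) / (1 - pq). The shift in the difference-in-difference is p minus this.

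| q | Odd-arm pre-rate | Shift | Share of 0.01 target |
|---|---|---|---|
| 10% | 0.0273 / 0.99697 = 0.0274 | 0.0030 | 30% |
| 25% | 0.02275 / 0.99242 = 0.0229 | 0.0074 | 74% |
| 50% | 0.01517 / 0.98483 = 0.0154 | 0.0149 | 149% |

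The shift counts against the sticker when the loss is in the odd arm. It would favour the sticker if the same loss fell in the even arm.

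**Number of buses involved.** 1060 x 0.0303 is about 32 buses with a pre-period crash per arm. The three values of q correspond to about 3, 8 and 16 of them, all well inside the buffer of 106.

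**Units.** If both the rate and the target are read per 1000, p is tiny and the shift is close to q x 0.0303 per 1000: 0.0030, 0.0076 and 0.0152. The ratio to the target barely changes.

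**Persistent risk.** Suppose buses that crashed before have k = 3 times the later risk of the others (an assumption). The others then have risk 0.03033 / (1 - 0.03033 + 3 x 0.03033) = 0.0286. With q = 50%, the odd-arm post-rate is 0.0286 x (0.96967 + 3 x 0.01517) / 0.98483 = 0.0295. That is 0.0009 below 0.0303, so the shift falls from 0.0149 to about 0.0141. Persistence shrinks the bias, though not by much at this value.

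**Could the balance check see it?** With 954 buses per arm, the standard error of the gap in pre-period rates is sqrt(2 x 0.0303 x 0.9697 / 954) = 0.0079. The three shifts are about 0.4, 0.9 and 1.9 standard errors.

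**The case against.** A reader might infer that the arms are in fact selected differently: that an even-plate bus needs no contact, and that an odd-plate bus off the road after a crash is missed. The article says neither. Both arms share the same eligibility criteria, the same enrolment target and the same 10% buffer, so even-plate buses can drop out too. That reading hangs largely on the word for considering even-plate buses in Randomization. An article may also leave the sampling frame to the full protocol, and the study-outline figures are not available here. This part of the objection stands, and the point is limited to what the design allows.

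It also stands that the loss fractions are invented, that one-sided loss is the extreme case, and that 50% would require half of such buses to be lost from one arm and none from the other. For big buses, full enrolment leaves little room for selection.

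The stated safeguards carry less weight. Data analysis compares past-year accident rates and pre-period claim rates between arms, adjusts for imbalance, and adds a sensitivity analysis controlling for baseline differences. Difference-in-difference also removes a gap between arms that is constant over time. But adjustment reaches only measured characteristics, the balance check would miss shifts of the smaller sizes above, and differencing does not remove selection on the pre-period outcome. It is what turns that selection into bias.

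**Conclusion.** The point holds in this form. Allocation by plate parity is systematic and unconcealed, so quasi-randomised is the accurate label. For minibuses the text expects losses during recruitment, asks only one arm to accept stickers, and words intention-to-treat by receipt, so nothing stated prevents differential selection.

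The shift of about 0.003 to 0.015 compared with a 0.01 target is hypothetical. For each assumed fraction it is an upper bound, because it takes loss from one arm only and no persistence of risk. It shows that a handful of buses could matter; it does not estimate the bias in this trial, and its direction depends on which arm loses them. No change in sample size follows from this point.

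**What to change.** Define the cohort from records, not from contact with the bus. The article notes that "RTSA maintains records of all PSVs", and insurers hold the cover and claims data. List all licensed, insured buses of both parities in the four towns at one common date before sticker placement. Analyse every listed bus by its assigned parity, with no exclusion after allocation, and reword the intention-to-treat sentence to say so. Describe the design as quasi-randomised in the title, abstract and Methods.

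This costs a register extract matched to insurer records, and no new field work. Odd-plate buses that never carried a sticker stay in their arm and dilute the estimate, a conservatism the article already accepts for its intention-to-treat analysis.

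If placement has not begun, allocate from the same roster by a computer-generated list stratified by vehicle type and town. The added cost is that inspectors work from a plate list instead of reading the last digit. The article records retrospective registration in November 2017, so this option may already be closed. The roster analysed by parity remains available either way, provided the records can be reconstructed as of the common date.
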